### Mental fatigue assessment

2.3

The mental fatigue will be assessed using a multidimensional approach, employing different complementary methods. These will include validated subjective instruments such as the FAS and the VAS, which will be administered digitally during Phase 2. The FAS, developed by Michielsen et al. (42) and validated for the Portuguese population by Alves and Nazaré (43), is recognized for its reliability, presenting high internal consistency (α = 0.870). It consists of 10 items on a 5-point Likert scale (1 = never, 5 = always) and assesses the perception of general fatigue. The items question the frequency of physical and mental symptoms of fatigue. This scale will only be applied at the beginning of the session, as it provides a stable measure of the general state of fatigue, suitable for the participants initial characterization. In turn, the VAS will be applied before and after the cognitive task, given its sensitivity to momentary variations in perceived mental fatigue. It is a single-item measure that asks participants to indicate the intensity of fatigue felt at the moment, by marking a point on a continuous line delimited by two extremes (no fatigue—extreme fatigue). For analysis, the marked position is converted into a continuous numerical measure (0–100). The use of this scale in Portugal is supported by national literature, namely in the studies by Afonso et al. (44) and Alves & Nazaré (43). Both will be administered digitally through the Google Forms platform, ensuring standardization and efficiency in data collection.

In parallel, during Phase 2, brain electrical activity will be recorded using the portable Emotiv Epoc Flex Gel Kit system, equipped with Ag/AgCl sensors arranged according to the international 10–20 system (32 channels), with reference and ground electrodes placed in standard positions. Data will be sampled at 128 Hz, ensuring impedances below 10 kΩ to guarantee signal quality. Each recording will have a total duration of five minutes, divided into three conditions: eyes open (two minutes), eyes closed (two minutes), and motor imagery (one minute). Participants will sit comfortably in a quiet environment to avoid external interference or movements that could generate artefacts. The selection of these three conditions is supported by evidence demonstrating that distinct neural states can be captured through resting conditions and motor imagery paradigms (45–47). Eyes-open and eyes-closed recordings are known to reflect different oscillatory dynamics, particularly in the alpha and theta bands (48, 49), while motor imagery reliably evokes measurable cortical activation and is sensitive to mental fatigue (50–52). In the statistical analyses, recording condition (eyes open, eyes closed, motor imagery) will be treated as a within-subject factor, allowing evaluation of whether fatigue-related changes differ across neural states.

To ensure data quality and reproducibility, EEG signals will undergo standardized pre-processing procedures. Data will be processed in MATLAB R2025a (MathWorks, Natick, MA, USA) using EEGLAB v2025. Continuous recordings will be visually inspected to identify gross artifacts or recording instabilities, and non-EEG channels will be removed prior to analysis. Signals will be band-pass filtered between 1 and 45 Hz using a zero-phase finite impulse response (FIR) filter and re-referenced to a common average reference. Artifact correction will be performed using Independent Component Analysis (extended infomax algorithm). Independent components will be automatically classified using the ICLabel plugin integrated in EEGLAB, and components identified as ocular, muscular, cardiac, line-noise, or other non-brain sources with high probability (≥0.90) will be removed prior to signal reconstruction. Channels exhibiting persistent excessive noise throughout the recording will be excluded from analysis. All preprocessing procedures will be applied consistently across participants and experimental conditions to ensure methodological standardization and internal validity.

Oculomotor activity will be recorded with the Pupil Core system (Pupil Labs GmbH, Germany), with sampling at 200 Hz. This equipment will allow the analysis of fixations, saccades, pupillary dilation or and blink rate, during the LSPT. The ETS was only applied in the LSPT, as it contains visual stimuli while performing gaze orientation and control of attention, appearing as especially appropriate to analyze gaze patterns (53). In addition, the LSPT is longer in duration, which makes it possible to collect consistent eye activity data. Vansteenkiste et al. (54) demonstrated a correlation between LSPT performance and gaze patterns in young players, reinforcing that this type of test is suitable for analyzing oculomotor metrics. In contrast, the Y-SART is a simple task and it presents brief visual stimuli, so the use of an eye-tracker is not justified. Recent research has demonstrated that motor skills (e.g., sprinting, changing direction, reactive strength) are the main determinant in performance on the Y-SART and is also affected by sensory/perceptual processes to a smaller extent or indirectly (55). The data will be processed with open-source software provided by the manufacturer.

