### Performance assessment

2.4

After collecting baseline data, participants will perform two motor tests as part of Phase 3 of the protocol. The first is the LSPT, which assesses passing accuracy and speed under time pressure in a standardized soccer-specific context. Participants perform 16 passes to designated targets announced in sequence, with performance assessed by total execution time adjusted for penalty points for technical errors (e.g., incorrect passes, errors in the target area, poor ball handling) and bonus points for accurate actions. This scoring protocol has been validated in youth and elite football players (56, 57). The test will be filmed with two cameras for subsequent technical analysis and penalty verification. A schematic representation of the LSPT setup is provided in Figure 2, adapted from Ali et al. (34).

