**Figure 3 F3:**
[figure not shown]
Schematic representation of the Y-SART, adapted from Yuan et al. (2).

After completing Phase 3, participants move on to Phase 4, where they perform the cognitive intervention defined by their group assignment, either the ST (experimental group) or a neutral task, such as reading magazines (control group). This is followed by Phase 5, which begins with participants completing the VAS again. Next, both motor tests are repeated, this time with continuous recording by the ETS. Finally, a second EEG recording is performed under the same conditions as in the initial phase, concluding the data collection session.

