##### VAS

2.5.4.2

The VAS for mental fatigue, applied immediately before and after the cognitive induction task (ST), captures acute fluctuations in the subjective perception of fatigue. This 100 mm continuous scale, anchored between “no fatigue” and “extreme fatigue”, is sensitive to short-term changes induced by cognitive load and task duration (84). Within the experimental group, VAS ratings will be compared pre and post ST to quantify the immediate impact of the intervention on mental fatigue.

In addition, associations between subjective fatigue and other objective markers will be explored. Specifically, post-intervention VAS results will be correlated with EEG spectral characteristics (particularly alpha and theta power), oculomotor parameters (blink rate, pupil diameter, saccadic dynamics, and fixations), and motor performance measures (LSPT and Y-SART). This approach allows us to determine whether higher levels of self-reported fatigue align with neurophysiological and behavioral indicators of reduced performance, providing a multimodal framework for validating the perceptual dimension of fatigue.

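### The VAS is named a mental-fatigue scale but its item and anchors ask about fatigue in general, so the within-group VAS change is not a clean check that the Stroop task induced mental fatigue

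*Protocol article*

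**What the plan says.** Section 2.3 chooses the VAS "given its sensitivity to momentary variations in perceived mental fatigue". It then describes one item that "asks participants to indicate the intensity of fatigue felt at the moment, by marking a point on a continuous line". The protocol gives the end points of this scale as "delimited by two extremes (no fatigue—extreme fatigue"). Section 2.5.4.2 opens with "The VAS for mental fatigue, applied immediately before and after the cognitive induction task (ST") and repeats the same two anchors, again without a mental qualifier.

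The other self-report scale, the FAS, is a baseline measure: "This scale will only be applied at the beginning of the session".

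On sequence, section 2.3 says of the FAS and VAS "which will be administered digitally during Phase 2". Section 2.4 then says that "participants will perform two motor tests as part of Phase 3 of the protocol". After these come 30 minutes of Stroop or magazine reading (Phase 4), and "This is followed by Phase 5, which begins with participants completing the VAS again", before the motor tests are repeated.

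On analysis, section 2.5.4.2 names a pre-post VAS comparison within the experimental group, and correlations of the post-intervention VAS with EEG, oculomotor and performance measures. Section 2.6 speaks of pre and post VAS comparisons. In general terms, for all outcomes, it also plans paired t-tests within each group and independent t-tests between groups at each time point.

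**The concern.** The construct named and the item described are not the same. An unqualified fatigue rating adds physical tiredness and sleepiness to mental fatigue. In this design the physical part is not negligible by construction, because every player completes a passing test and an agility test before the second rating.

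Two uses of the VAS are exposed. One is the within-experimental-group change, which section 2.5.4.2 uses to quantify the immediate impact of the Stroop task on mental fatigue. The other is the set of VAS correlations. Section 2.5.1 states that the EEG changes are not specific to mental fatigue, and section 2.5.1.2 says they will be read together with behavioural, oculomotor and subjective measures. The self-report is thus expected to add specificity, but its item does not name the construct. Section 2.3 itself says that motor skills are the main determinant of Y-SART performance. Residual physical tiredness could therefore affect both the rating and the Y-SART time, and produce an association that is then read as mental fatigue.

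**Working it through.** **The plan's own figure.** The point has no figure of its own in the protocol; the only one used is the group size. Section 2.2 gives 34 players (17 per group) for a two-group, two-time repeated-measures ANOVA with f = 0.25, alpha 0.05 and power 80%. Assuming a pre-post correlation of 0.5, which the article does not state, the noncentrality is f² × N × m / (1 − rho) = 0.0625 × 34 × 2 / 0.5 = 8.5 on 1 and 32 degrees of freedom. Power is 0.807, and 34 is the smallest even N that reaches 0.80. The figure reproduces, so n = 17 per group is used below.

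**What enters the change score under each timing.** Sections 2.3 and 2.5.4.2 place the first rating differently.
- First rating in Phase 2 (2.3): both motor tests fall between the two ratings. Any tiredness that remains after 30 minutes seated raises the change.
- First rating immediately before the Stroop task (2.5.4.2): no motor test falls between the ratings. The first one follows the tests, so recovery while seated lowers the change and can hide a real rise.

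Under either timing a general item carries a physical component. Settling the timing alone would change its direction but would not remove it.

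**Illustration 1: false positives in the within-group test.** Assumptions not in the protocol: no mental-fatigue effect, a motor-test shift c of 5 to 15 VAS points equal in both arms, and an SD of change of 15 to 25 points. For the paired t-test with n = 17, the noncentrality is c / (SD / √17) on 16 degrees of freedom, two-sided at 0.05. At SD 20 the standard error is 20 / 4.123 = 4.85, so c = 10 gives 10 / 4.85 = 2.06.

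| SD of change | c = 5 | c = 10 | c = 15 |
|---|---|---|---|
| 15 | 0.253 | 0.733 | 0.972 |
| 20 | 0.163 | 0.491 | 0.827 |
| 25 | 0.121 | 0.341 | 0.642 |

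These are probabilities of a significant within-group change with no mental-fatigue effect; the nominal value is 0.05. For the comparison between arms, c cancels and the probability stays at 0.05 in every cell.

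**Illustration 2: dilution.** Assume a mental component with SD 15, a true Stroop effect of 20 points, and independent physical tiredness with SD 10 to 20; none of these is in the protocol.
- Total SD: √(15² + 10²) = 18.0 to √(15² + 20²) = 25.
- Standardised effect: 20/15 = 1.33 falls to 20/18.0 = 1.11, or to 20/25 = 0.80.
- The correlation with a marker that depends on mental fatigue only is multiplied by 15/18.0 = 0.83 to 15/25 = 0.60.

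A measure that is itself affected by physical tiredness can instead show an inflated correlation.

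**The case against.** The strongest reply is randomisation. Both arms do the same Phase 3 tests and then a 30-minute task, and the hypothesis in the Introduction is stated against the low-load control. Section 2.6 plans between-group t-tests, and the Discussion describes a repeated-measures ANOVA for the time and group interaction. A motor-test effect common to both arms does not bias these comparisons. This stands in full. A reader might infer that the VAS cannot show any induced mental fatigue; the documents do not support that. A higher rating after Stroop than after reading would be an effect of the task. What remains is that a general item cannot say whether such a difference is mental fatigue or sleepiness.

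Second, a reader might picture players rating themselves straight after exercise. They do not: the second rating follows the Phase 3 tests by at least 30 minutes and comes before the tests are repeated. The physical component may therefore be small.

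Third, the article describes the item and does not reproduce the participant-facing form. A heading or instruction there may already say mental fatigue. This is possible, and the fix allows for it. However, the item content is given once and the anchors twice, neither with the qualifier, so the text as it stands needs correcting in either case.

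Fourth, the SDs and shifts above are assumed, and a change score removes stable differences between players. Illustration 2 shows dilution, not inability to detect an effect. Nor does causal attribution rest on the VAS alone: it rests on random assignment, with several modalities read together.

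**Conclusion.** The point holds in a limited form. As described, the item and anchors do not match the construct that the protocol names. Since the VAS is the only repeated self-report, its pre-post change within the experimental group is not a clean manipulation check, and its correlations may mix physical tiredness with mental fatigue. Under the assumptions stated, the within-group test can be significant with probability 0.12 to 0.97 when no mental fatigue was induced, and correlations with a purely mental marker shrink to 0.83 to 0.60 of their value. These ranges show the mechanism and do not predict what this trial will find, because the protocol gives no VAS variability and no estimate of the physical carry-over.

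The between-group contrast remains valid as a test of Stroop against reading. The defect is one of construct validity and of which comparison is named for the VAS; it does not undermine the randomised comparison.

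**What to change.** In 2.3 and 2.5.4.2, word the item and both anchors as mental fatigue, for example *How mentally fatigued do you feel right now?*, from *no mental fatigue* to *extreme mental fatigue*. Use it in both arms at each administration. If the actual prompt already says this, correct the description in both sections. Optionally add a second line for physical fatigue in the same format, so that the two can be separated in the correlations.

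In 2.5.4.2 and 2.6, name the between-group VAS contrast as the induction check and keep the within-group change as descriptive. When these sections are edited, also reconcile the timing of the first rating, since the two sections differ on it.

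The cost is an edit to one item in a digital form and a few sentences of text. The abstract states that no data are yet available, so the change can still be made; an unqualified rating cannot be split into its components afterwards. The downside is slightly looser comparability with earlier uses of the unqualified anchors.

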##### Selection and justification of EEG channels

2.5.1.1

Electrodes F3, F4, Fz, C3, C4, Cz, P3, P4, Pz, T3, T4, T5, T6, O1, O2, and Oz will be analysed according to the international 10–20 system, allowing comprehensive coverage of the frontal, central, parietal, temporal, and occipital regions. The frontal, central, and parietal regions are particularly sensitive to the effects of mental fatigue, showing increases in theta band power and reductions in alpha band power, phenomena associated with greater attentional effort and decreased cognitive efficiency (19, 61, 62). The temporal and occipital regions were included to ensure a comprehensive characterisation of cortical activity, as previous studies have identified changes in functional connectivity and neural complexity associated with sensory integration and visuospatial regulation under fatigue (62).

Based on explicit theoretical hypotheses, frontal midline electrodes (particularly Fz and adjacent frontal sites) are defined as primary regions of interest (ROIs), given the well-established association between frontal theta activity and mental fatigue. Posterior parietal-occipital regions are included due to their documented involvement in alpha modulation and attentional processing under cognitive load. Analyses focusing on these predefined ROIs and frequency bands (theta, alpha, beta) will be considered primary. Analyses involving additional scalp regions will be clearly identified as exploratory and interpreted with appropriate caution.

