### Statistical analysis

2.6

All statistical analyses will be performed using IBM SPSS Statistics version 29.0 (IBM Corporation, Armonk, NY, USA), with a significance level set at 5% (*p* < 0.05). Descriptive statistics (mean, standard deviation, 95% confidence intervals, and range) will be calculated for all outcome variables, including EEG spectral powers, oculomotor parameters, motor performance scores, and subjective fatigue ratings. These data will be stratified by group (experimental and control) and time (pre- and post-intervention) and presented visually using box plots and line graphs to facilitate interpretation (88, 89).

To assess the effect of mental fatigue, paired t-tests will compare pre- and post-intervention results within each group, while independent t-tests will compare the experimental and control groups at each time point (88, 90). For EEG outcomes, repeated-measures ANOVA models will include Time (pre vs. post mental fatigue) and Recording Condition (eyes open, eyes closed, motor imagery) as within-subject factors, and Group (experimental vs. control) as a between-subject factor (88, 90). Assumptions of normality and sphericity will be evaluated prior to analysis, following established recommendations for repeated measures designs (88, 91). When sphericity is violated, the Greenhouse-Geisser correction will be applied. Effect sizes will be reported using eta squared (*η*^2^), interpreted according to Marôco (90) as small (<0.04), moderate (0.04–0.25), or large (≥0.25). Statistical power (π) will also be reported when applicable (92, 93).

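### Visual inspection and channel exclusion for the primary EEG analyses rest on judgement, and no masking to arm or time point is stated

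*Protocol article*

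**What the plan says.** Section 2.3 (Mental fatigue assessment) sets out the EEG processing: named software versions, a 1 to 45 Hz filter, a common average reference and independent component analysis. Artefact correction follows a rule: "Independent components will be automatically classified using the ICLabel plugin integrated in EEGLAB", with removal of non-brain components at a probability of at least 0.90.

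Two other steps have no such rule:

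- "Continuous recordings will be visually inspected to identify gross artifacts or recording instabilities".
- "Channels exhibiting persistent excessive noise throughout the recording will be excluded from analysis".

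The safeguard offered for the whole pipeline is this: "All preprocessing procedures will be applied consistently across participants and experimental conditions to ensure methodological standardization and internal validity".

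Section 2.5.1.1 lists 16 electrodes for analysis and names the frontal midline sites, particularly Fz and its neighbours, as primary regions of interest, with posterior regions also included. It then says: "Analyses focusing on these predefined ROIs and frequency bands (theta, alpha, beta) will be considered primary". Section 2.6 repeats that the primary EEG analyses are on the frontal midline and posterior regions. The model has Time and Recording Condition within subject and "Group (experimental vs. control) as a between-subject factor".

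No section mentions masking of anyone.

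**The concern.** The two judgement steps come before the analyses that the article labels primary. If the person who inspects the recordings and drops channels knows the arm and whether a recording is pre or post, expectation can affect what is kept. The contrast of interest, the difference between arms in pre-post change, is exposed to exactly that kind of differential decision.

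Three features of the plan make the point worth settling:

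- **Few frontal electrodes.** Only F3, F4 and Fz in the analysed list are frontal, so dropping one channel removes a large part of the frontal region in that recording.
- **Noisier equipment.** Section 2.5.1 concedes that the device has a poorer signal-to-noise ratio and lower reliability than medical-grade systems. Borderline channels are therefore foreseeable.
- **Recording order.** By section 2.4, the second EEG follows the repeated motor tests, whereas the first precedes any motor test. Noise, and so cleaning decisions, may cluster in the post recordings. This holds in both arms and is not itself a bias between them, but it leaves more to judge at the time point that matters.

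**Working it through.** **1. Which steps rest on judgement**

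| Step in section 2.3 | Criterion stated | Masking stated |
|---|---|---|
| Visual inspection for gross artefacts or instabilities | None numerical | No |
| Filter and re-reference | Fixed settings | Not needed |
| Component removal (ICLabel) | Probability at least 0.90 | Not needed |
| Channel exclusion | Persistent, excessive, throughout the recording; no number | No |

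Only the first and last rows depend on who is looking. Of these, only channel exclusion is expressly said to remove data; inspection is said only to identify problems.

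**2. Weight of one channel**

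The analysed list has F3, F4 and Fz as its frontal sites. If the frontal region were the average of these three (an assumption, since the article does not close the list), excluding one removes 1/3 of it. If Fz is dropped at post but kept at pre, that participant's change score mixes a change of site with a change over time.

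**3. The plan's own sample size**

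Section 2.2 gives f = 0.25, alpha 0.05, power 80% and 34 participants (17 per group) for two groups and two times. The pre-post correlation is not given; assume rho = 0.5. For the group-by-time interaction:

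lambda = f² × N × m / (1 − rho) = 0.0625 × 34 × 2 / 0.5 = 8.5, on 1 and 32 degrees of freedom.

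Power is 0.807, so 34 is reproduced. Nothing here disputes the sample size.

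**4. What a differential cleaning bias would do**

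At f = 0.25 the four cell effects are ±0.25 SD, so the planned difference in change is 4 × 0.25 = 1.0 SD. The SD of a change score is √(2(1 − rho)) = 1.0 at rho = 0.5 and 0.775 at rho = 0.7. For a bias b in the difference in change, the two-sample t statistic has noncentrality b / (SD of change × √(2/17)) on 32 degrees of freedom. The values of b are assumptions; the article gives none.

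| Bias b (SD) | False-positive rate, rho 0.5 | False-positive rate, rho 0.7 | Power if the true effect is 1.0 SD and bias opposes it, rho 0.5 |
|---|---|---|---|
| 0 | 5.0% | 5.0% | 80.7% |
| 0.1 | 5.9% | 6.5% | 72.1% |
| 0.25 | 10.9% | 15.0% | 56.4% |
| 0.5 | 29.3% | 44.7% | 29.3% |

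**5. A segment-removal illustration, and why it carries little weight**

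Assume 2-second epochs, theta power per epoch distributed as chi-square(12)/12, a log-change SD of 0.2 to 0.4, and removal of the highest-theta epochs from one arm's post recording only.

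- Removing 5% leaves 0.946 of mean theta. The shift is 0.055 in logs, or 0.14 to 0.28 SD of change, and the two-sided false-positive rate is 6.8% to 12.2%.
- Removing 10% leaves 0.908. The shift is 0.097 in logs, or 0.24 to 0.48 SD, and the rate is 10.5% to 27.7%.

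The protocol describes neither epochs nor segment rejection, and the removal assumed is wholly one-sided. Direction matters too. Trimming the Stroop arm lowers its theta, and the chance of a false result of higher theta then falls from 2.5% to 0.3%–0.9% at 5% removal. Only trimming the control arm would favour higher theta. These figures show a mechanism and do not estimate a bias.

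**The case against.** The best reply is that the article is silent on masking, which is not the same as saying that the cleaner sees arm and time point. A condensed article may leave file handling to a fuller document. This stands in part: a reader might infer unmasked cleaning, but the text does not say so. The point survives because section 2.3 does not merely omit the matter. It gives the pipeline in detail and rests internal validity on consistent application, which cannot deliver it for a step with no criterion.

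Four further limits also stand:

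- **Discretion is narrow.** Inspection is for gross artefacts, exclusion is for noise lasting throughout the recording, and the main artefact removal is automated at a fixed cut-off.
- **Segment deletion is not stated.** A reader might take visual inspection to decide which stretches of data enter the analysis; the text says only that problems are identified.
- **The hypothesis is not directional for theta.** A reader might infer that the study bets on frontal theta rising. The Introduction's hypothesis is altered frontal-parietal activity, and the Abstract expects changes in oscillatory activity. Rises in theta appear as background from the literature, with the caution that they are not specific to fatigue.
- **Creating or erasing the Stroop effect is not shown.** Cancelling the planned effect would need a bias of about 1.0 SD at the design assumptions, and even the extreme illustration reaches only 0.48 SD.

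**Conclusion.** The point holds in a limited form. Visual inspection and channel exclusion are judgement steps before the primary EEG analyses, channel exclusion has no numerical limit, and the article states no masking to arm or to pre/post for either. The assurance of consistent application does not fill that gap. Automated component removal is outside the criticism.

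The size of any bias is unknown and cannot be derived from the article. The table in step 4 shows only that, with 17 per arm, a differential shift of a quarter of an SD would roughly double the false-positive rate (10.9% against 5.0%) at an assumed correlation of 0.5. The protocol should be changed because the protection is nearly free and cannot be restored once cleaning has been done with arm and time point in view.

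**What to change.** In section 2.3, state that:

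1. before any cleaning, all EEG files are renamed with random codes that hide arm and time point;
2. visual inspection and channel exclusion are done on the coded files, with channel exclusion judged against a numerical noise criterion fixed beforehand;
3. the list of exclusions is locked before the codes are opened.

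Reporting excluded channels by arm and time point would let readers see whether cleaning was balanced.

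The cost is a renaming script and a sentence in 2.3, plus agreement on the noise criterion. Sample size, procedures and staff do not change.
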